## Abstract

**Background:**

Surgery for colorectal cancer is associated with a high risk of post-operative adverse events, re-operations and a prolonged post-operative recovery. Previously, the effect of prehabilitation (pre-operative physical activity) has been studied for different types of surgery, including colorectal surgery. However, the trials on colorectal surgery have been of limited methodological quality and size. The aim of this trial is to compare the effect of a combined pre- and post-operative intervention of moderate aerobic physical activity and inspiratory muscle training (IMT) with standard care on post-operative recovery after surgery for colorectal cancer.

**Methods/design:**

We are conducting a randomised, controlled, parallel-group, open-label, multi-centre trial with physical recovery within 4 weeks after cancer surgery as the primary endpoint. Some 640 patients planned for surgery for colorectal cancer will be enrolled. The intervention consists of pre- and post-operative physical activity with increased daily aerobic activity of moderate intensity as well as IMT. In the control group, patients will be advised to continue their normal daily exercise routine. The primary outcome is patient-reported physical recovery 4 weeks post-operatively. Secondary outcomes are length of sick leave, complication rate and severity, length of hospital stay, re-admittances, re-operations, post-operative mental recovery, quality of life and mortality, as well as changes in insulin-like growth factor 1 and insulin-like growth factor-binding protein 3, perception of pain and a health economic analysis.

**Discussion:**

An increase in moderate-intensity aerobic physical activity is a safe, cheap and feasible intervention that would be possible to implement in standard care for patients with colorectal cancer. If shown to be effective, this lifestyle intervention could be a clinical parallel to pre-operative smoke cessation that has already been implemented with good clinical results.

**Trial registration:**

ClinicalTrials.gov identifier: NCT02299596. Registered on 17 November 2014.

**Electronic supplementary material:**

The online version of this article (doi:10.1186/s13063-017-1949-9) contains supplementary material, which is available to authorized users.

## Background

All surgical procedures are followed by a phase of post-operative recovery, which typically includes both individual distress and consumption of health care resources. Recovery after colon and rectal cancer surgery is known to include a high level of post-operative adverse events, with reported rates up to 35%, re-operation rates of around 10% and 30-day mortality of around 2% [1–3]. The Swedish National Board of Health and Welfare estimates that, without complications, most patients with colon cancer return to normal function within 4–6 weeks post-surgery, whereas rectal cancer patients require a longer time to recover, up to 6–8 weeks [4, 5].

Prospective observational studies have shown that physical activity before and after a colorectal cancer diagnosis as well as after treatment is associated with better survival [6–8]. This is plausible because the multiple effects of physical activity include effects on endurance, strength and functional capacity; mental and stress-related health and quality of life (QoL) [9]; immune function [10]; and cardiovascular morbidity and mortality [9]. Possibly contributing mediators of this effect include insulin-like growth factor (IGF)-1 and insulin-like growth factor-binding protein (IGFBP)-3 [11, 12]. Researchers in one small randomised controlled trial (RCT) reported effects of post-operative physical activity on the IGF axis with a significant increase in IGF-1 and IGFBP-3 in stages II–III colorectal cancer survivors [13], which could be of benefit for the patient.

In previous studies evaluating prehabilitation with pre-operative physical activity before colorectal cancer surgery [14–17], researchers reported effects on functional exercise capacity, but their studies did not have enough power to detect any effects on adverse events or recovery. In one study, researchers found positive effects on walking capacity in the group performing the ‘sham’ intervention, consisting of walking, compared with the group that performed more intense physical activity [14], probably partly due to lower compliance with more intense activity. Authors of a recent systematic review of prehabilitation before colorectal cancer surgery concluded that there is currently no clear evidence that an improvement in fitness translates into improved peri- and post-operative outcomes. It was further concluded that further adequately powered RCTs are needed to investigate whether pre-operative exercise improves post-operative morbidity and mortality [18]. Authors of another recent systematic review on prehabilitation and abdominal cancer surgery concluded that previous trials in this area suffer from methodological heterogeneity [19]. All trials in their systematic review had functional capacity measures as their primary outcome measures. In a third recent systematic review on prehabilitation and abdominal surgery, it was concluded that prehabilitation appears to decrease post-operative complications after abdominal surgery but that more high-quality studies are needed [20]. To summarise, there have been several trials assessing the effect of prehabilitation and abdominal surgery, but they have been of relatively small size, and their primary outcome measures have been to assess the effect on functional capacity measures rather than on outcome measures of clinical post-operative recovery.

There are other areas of surgery where there is evidence of positive effects from pre-operative physical activity (e.g., thoracic surgery) [21–24]. Inspiratory muscle training (IMT) is one type of physical activity that has been found to be successful in reducing post-operative pulmonary complications and hospital length of stay [22].

Our hypothesis to be tested in the present study is that individuals receiving an intervention aimed at increasing their pre- and post-operative level of physical activity of moderate intensity will experience faster post-operative recovery in comparison with standard care. The primary aim of this study is to investigate whether a training programme with intensified physical activity and IMT prior to and after surgery for colorectal cancer enhances post-operative recovery assessed as patient-reported physical recovery in comparison with control subjects. Secondary aims are to investigate the effect of the training programme on sick leave, adverse events, hospital length of stay, resumption of QoL, re-operations, re-admittances, post-operative mental recovery, mortality, IGF-1, IGFBP-3, experienced pain and health economics in comparison with control subjects.

## Methods/design

This study is a randomised, controlled, parallel-group, open-label, multi-centre trial. The primary endpoint is physical recovery 4 weeks after surgery. The locations of the study are university and county hospitals in Sweden that regularly perform colorectal surgery. At the moment, two hospitals participate in the study, but more centres may be added. A list of study sites can be obtained from the corresponding author. Eligible participants are all patients aged 20 years or older scheduled for elective colorectal cancer surgery in the participating hospitals during the inclusion period. Informed consent forms will be signed and dated prior to conduct of any study-specific procedures. Exclusion criteria are emergency surgery, local surgery such as transanal endoscopic microsurgery, cytoreductive surgery and subsequent hyperthermic intraperitoneal chemotherapy, as well as patients unable to understand information given or who are considered unable to perform study-specific procedures.

### Groups

The intervention and control groups will differ with regard to both pre- and post-operative care in the outpatient setting. During the hospital stay, both groups will be treated according to standard care. In the intervention group, patients perform the following intervention pre-operatively during 2 weeks ± 4 days:
*Thirty minutes of daily aerobic exercise added to the normal daily exercise routine of each patient:* The type of aerobic exercise is chosen by the patient, and the exercise is performed in the home environment. The level of exercise should produce shortness of breath, but the patient should be able to talk without much effort, corresponding to relative medium-intensity activity for the individual, according to Borg’s Rating of Perceived Exertion Scale [25].
*IMT:* The patient’s maximal inspiratory pressure (MIP) is assessed by a physiotherapist at residual volume with a MicroRPM respiratory pressure meter (CareFusion, Höchberg, Germany). The assessment is performed with the patient sitting, and the best result of at least three is noted [26]. The IMT is performed with a Threshold IMT device (Philips Respironics, Eindhoven, The Netherlands). Starting with a resistance of 30% of MIP, the patient is instructed on how the resistance can be increased if needed. The patient is instructed to perform 30 breaths two times, twice daily.

During hospitalisation post-surgery, patients in both groups receive standardised information from a physiotherapist starting on the first day after surgery, including breathing exercises with positive expiratory pressure by mouthpiece (open procedures) or deep breaths (laparoscopic procedures) every 2 h during the daytime, as well as early and frequent mobilisation. The including hospitals may adhere to different extents to the Enhanced Recovery After Surgery (ERAS) protocol [27], but they are instructed to treat all patients according to local routine, regardless of randomisation allocation. The hospital’s adherence to the ERAS protocol will be reported. Hospital staff are not actively informed about the patient’s allocation.

Post-operatively, from the time of discharge from hospital and for four weeks, patients in the intervention groups perform the following:
*Thirty minutes of daily exercise added to the normal daily exercise routine of each patient:* The level of exercise should produce shortness of breath, but the patient should be able to talk without much effort [25].

A research nurse will contact patients in the intervention group by phone 1 week into the pre-operative intervention and 3 weeks into the post-operative intervention to ascertain that the physical activity and IMT are progressing as planned, with possibility for modifications. To improve and monitor adherence to the intervention, all patients in the intervention group fill in an exercise diary on a daily basis pre-operatively as well as up to 4 weeks after discharge from hospital, where instructions are clearly outlined for the intervention group. In the control group, patients will be advised to continue their normal daily exercise routine. Patients in the control group will receive a similar diary where they will register their physical activity, but without specified goals or instructions.

### Outcomes

The primary endpoint is physical recovery as measured by patient-reported experienced physical recovery. Patient-reported physical recovery will be assessed by questionnaires 4 weeks and 1 year post-operatively, with the question, “To what extent do you feel fully physically recovered”? Answering categories are 0%, 25%, 50%, 75% and 100%. This question has been validated face-to-face and has previously been used in several cohort studies [28–30].

Secondary endpoints are as follows:
*Sick leave:* This will be measured by length and degree of sick leave, for all causes, during the first year post-operatively.
*Adverse events classified according to the Clavien-Dindo classification of surgical complications* [31] *within the first 90 days post-operatively:* These will be reported as the number of complications grade O-IIIa and IIIb-V. We will also report information gained from the comprehensive complications index for all patients, which is derived from the Clavien-Dindo classification [32].
*Length of hospital stay*

*Post-operative recovery of QoL measured with several instruments pre-operatively and 4 weeks and 1 year post-operatively:* Quality-adjusted life-years (QALYs) will be possible to calculate because EQ-5D is included in the questionnaire [33].
*Re-operations and re-admittances within the first 12 months after primary surgery:* All forms of surgery and all re-admissions to hospital will be registered.
*Patient-reported experienced mental recovery 4 weeks and 12 months post-operatively, used in previous observational cohort studies* [28–30]
*Post-operative all-cause and cancer-specific mortality, measured at 3 and 5 years*

*Changes in IGF-1, IGFBP-3 and glycated haemoglobin (HbA1c) levels from baseline to time of surgery (IGF-1 and IGFBP-3) and 4–6 weeks after surgery (all):* These will be determined for a subgroup of the patients and analysed prior to the rest of the outcomes.
*Post-operative pain measured with Brief Pain Inventory–Short Form (BPI-SF):* This will be measured 4 weeks and 12 months post-operatively [34].
*Health economic analysis of resource consumption 12 months post-operatively:* This will be performed separately, depending on other outcomes.

### Questionnaires used in this study

The pre- and post-operative questionnaires (4 weeks and 12 months post-operatively) in this study are composed mainly of the following well-established questionnaires:
*The International Physical Activity Questionnaire (IPAQ)* [35]*:* a validated questionnaire for assessing level of physical activity that consists of seven questions
*Saltin-Grimby Physical Activity Level Scale* [36]*:* A single question that has been shown to have high validity and reliability, being associated with cardiovascular risk factors [37, 38], morbidity [39, 40] and mortality [41]
*RAND-36, also known as the 36-item Short Form Health Survey, or SF-36* [42]*:* A health profile survey with high clinical validity [43] that consists of 11 questions with several sub-questions and a total of 36 items
*Health-related QoL:* Assessed with the well-established form EQ-5D [44], which consists of six questions; this can also serve as a basis for calculating QALYs [33]
*Sense of coherence:* Questions for assessing how individuals experience themselves in relation to their environment [45], assessed with 29 questions
*Alcohol Use Disorders Identification Test alcohol consumption questions (AUDIT-C)* [46]*:* Alcohol use is assessed using this instrument, which is a screening tool for problem drinking and consists of three questions.
*Pain:* Assessed using the BPI-SF questionnaire [34], consisting of 15 questions regarding different aspects of pain

### Allocation

A research nurse will perform enrolment and the electronic randomisation. The trial is an open-label study because neither patients nor research nurses nor physiotherapists can be blinded. However, registration regarding complications, hospital length of stay, re-operations, re-admittances, mortality and sick leave will be blinded. The nurses and surgeons responsible for providing care during the hospital stay are not actively informed about allocation. Randomisation will be performed as block randomisation with a 1:1 allocation and a block size that will be unknown to study personnel. To ensure good balance of participant characteristics in each group, randomisation will be stratified with regard to surgical method (laparoscopic versus open), tumour site and pre-operative treatment (colon, rectum with/without radiotherapy), and study centre. Randomisation numbers (patient numbers) will be assigned strictly sequentially as patients become eligible for randomisation. The assigned group is automatically generated and cannot be changed retrospectively.

The screening log and randomisation process is part of an electronic clinical record form in which inclusion and exclusion criteria are noted, as well as information needed for stratification. All patients planned for elective colorectal surgery at participating hospitals are included in the screening log. Patients excluded will be included in the screening log with information on age, sex and reason for exclusion.

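### If the undisclosed block size is fixed, an unblinded research nurse who enrols and randomises could infer it and foresee up to a fifth to a third of allocations; randomly varying sizes would remove most of that certainty

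*Protocol article*

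**What the plan says.** All the structural elements are in the protocol article.

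- **Who enrols and randomises.** Allocation: "A research nurse will perform enrolment and the electronic randomisation". Under Sample size, a research nurse also gives patients oral information at the pre-operative outpatient visit.
- **Blinding.** Allocation: "The trial is an open-label study because neither patients nor research nurses nor physiotherapists can be blinded".
- **Sequence.** Allocation: "Randomisation will be performed as block randomisation with a 1:1 allocation and a block size that will be unknown to study personnel". No size is given, and the text does not say whether it is fixed or varies.
- **Strata.** Allocation: "randomisation will be stratified with regard to surgical method (laparoscopic versus open), tumour site and pre-operative treatment (colon, rectum with/without radiotherapy), and study centre". Methods/design: "At the moment, two hospitals participate in the study, but more centres may be added".
- **Discretion before randomisation.** The exclusion criteria in Methods/design include "patients unable to understand information given or who are considered unable to perform study-specific procedures".
- **Other safeguards.** Allocation: "The assigned group is automatically generated and cannot be changed retrospectively". Excluded patients are entered in a screening log with age, sex and reason.

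**The concern.** Keeping the block size from staff protects the next assignment only while staff cannot work it out. In an open-label trial the person who enrols also sees what each patient received. With fixed blocks inside a centre-level stratum, the two arms return to equality at regular intervals, and those intervals reveal the size. Once it is known, the end of each block can be foreseen.

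A nurse who foresees the next assignment could, knowingly or not, encourage a frail patient less, or apply the judgement-based exclusion more readily, when the exercise arm is next. The groups would then differ in fitness before treatment begins. The Statistical methods section adjusts for the stratification factors, but these do not include fitness, so selection within a stratum would remain.

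The primary endpoint is a patient's own rating of physical recovery (Outcomes). It is not among the outcomes listed in Allocation as registered blind. Unpredictable allocation is therefore one of the main protections this endpoint has.

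**Working it through.** **The plan's own figures.** The article gives no figure for block size or predictability. The total of 640 is used here only for scale, and it reproduces. For 49% versus 37%, two-sided 2.5% and 80% power, n per arm = [2.2414 × √(2 × 0.43 × 0.57) + 0.8416 × √(0.49 × 0.51 + 0.37 × 0.63)]² / 0.12² = 322.3. This rounds up to 323 per arm or 646 in total; 320 per arm gives 79.7% power.

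**Step 1: strata.** Two surgical methods × three site/radiotherapy groups = 6 strata per centre. With two centres there are 12. On average 640 / 12 = 53.3 patients fall in each, if strata are equal. Completed blocks per average stratum: 13 for size 4 (53.3 / 4 = 13.3), 8 for size 6 (8.9) and 6 for size 8 (6.7).

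**Step 2: share foreseeable if the size is fixed and known.** In a 1:1 block of size B = 2h, allocations are determined once one arm is used up. The expected number determined per block is 2h/(h + 1), so the share is 1/(h + 1) = 2/(B + 2). As a check for B = 4, the six possible orders have determined tails of 2, 1, 1, 2, 1 and 1. Their mean is 8/6 = 1.33 of 4, or one third.

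| Fixed size (assumed) | Share certain | Of 640 | Best-guess accuracy |
|---|---|---|---|
| 4 | 33% | 213 | 71% |
| 6 | 25% | 160 | 68% |
| 8 | 20% | 128 | 67% |

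Best-guess accuracy is the proportion correct when the observer always guesses the arm that is behind in the current block, and tosses a coin when the arms are level.

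**Step 3: how quickly a fixed size could be inferred.** Assume an observer who sees a stratum from its first patient and considers the even sizes 2 to 10. In simulation, all sizes smaller than the true one are ruled out after a median of 6, 8 or 12 patients for true sizes 4, 6 or 8, which is under two blocks in each case. Multiples of the true size are never strictly ruled out, so the inference is strong but not certain.

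**Step 4: the same measures with varying sizes.** Simulated strata of 53 patients, block sizes equally likely, and an observer who knows the set of sizes and tracks every allocation:

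| Sizes | Share certain | Best-guess accuracy |
|---|---|---|
| 4 and 6 at random | 5% to 6% | 69% |
| 4, 6 and 8 at random | 2% | about 68% |

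On 640 patients, 2% to 6% is about 13 to 38 allocations. The same simulation with fixed size 4 or 6 returns 33% and 24%, in line with step 2.

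**The case against.** The strongest reply is that the article never declares a fixed size. The singular is a hint and no more. Withholding block details from staff, and therefore from a public article, is good practice, and a condensed article may leave the question of varying sizes to the full protocol or the randomisation specification. This stands, and it is why the point is conditional. It does not dispose of it: the wording that describes the safeguard reads most naturally as one size, and a statement that sizes vary would disclose nothing useful to sites.

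A reader might go further and infer that allocations become certain before consent. The documents do not support that. It would need a fixed size, and one nurse (or shared records) following every allocation across six interleaved strata per centre. The number of nurses is not given. The shares in step 2 also assume the size is known from the first patient, and further centres would make the strata smaller.

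The existing safeguards deserve weight. Assignment is electronic, sequential and irreversible. The screening log records exclusions. Patients receive a telephone call and written information before the visit (Sample size). Deferral is limited by the operation date and the pre-operative intervention window (Groups). Questionnaires at inclusion cover physical activity and health status (Data collection), so an imbalance in fitness could be noticed. These limit or expose the consequences; none prevents prediction of the next assignment. The log carries no measure of fitness, so selective exclusion would be hard to see there.

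A reader might also infer that nurses are steering patients, or that the result is already biased in favour of exercise. Nothing in the article shows either. The direction described above is a plausible one, not an observed one.

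Finally, varying the sizes is only a partial remedy. Best-guess accuracy hardly moves, and someone acting on the running imbalance could still do better than chance. This stands in full.

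**Conclusion.** The point holds as a conditional design weakness. If the block size is fixed, the stated safeguard is weak in an open-label trial stratified by centre in which an unblinded nurse informs, enrols and randomises. Up to 33%, 25% or 20% of allocations could be foreseen for sizes 4, 6 or 8. These upper bounds rest on an assumed size, an observer who follows the stratum, and no allowance for learning. If sizes already vary at random, the share is about 2% to 6% and only the wording is at fault.

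The point concerns opportunity; the article gives no evidence that allocation has been subverted. It merits action because the change is cheap and the primary endpoint is self-reported by unblinded patients.

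**What to change.** For patients still to be randomised, and for any added centre, set the electronic system to draw block sizes at random from several undisclosed sizes within each stratum. In Allocation, replace *a block size* with *randomly varying block sizes, not disclosed to sites*. If the system already does this, only the sentence changes. Recruitment was ongoing according to Trial status, so the change can still take effect; it cannot alter assignments already made.

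The cost is a system setting and one sentence, with no additional patients or staff. The downside is slightly larger possible imbalance within strata. The change should be presented as removing most of the certainty about upcoming assignments, not as making them unpredictable.
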